#### **Treatment of intermittently missing HIV-1 RNA assessments.**

The key visits in the definition of the virological components of the primary endpoints are weeks 18, 24 and 32. If week 18 or week 24 visit was missed then the assessment as to whether insufficient response at this visit had occurred will be based on whether the regimen was changed at the next attended visit (week 24 or week 32). If all three visits (W18, W24 and W32) were missed and the primary endpoint was not reached at the last attended visit before W18, then the follow-up will be censored at W18 regardless of whether the patient had attended after W32. If only W32 visit was missed and the primary endpoint had not been reached before W32, then HIV-1 RNA measurement is to be performed as soon as possible and no later than W40. In that case virological failure at W32 will be assessed according to the level of HIV-1 RNA at the extra measurement (W40). If HIV-1 RNA level was missing at both W32 and W40 then follow-up will be censored at W32.

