### 3.1 Primary endpoint

The primary endpoint is time to virologic or clinical failure, defined as the first occurrence of any of the following six components:

- Component 1: failure to achieve virologic response by W32 (defined as HIV-1 RNA  $\geq$  50 copies/ml at W32, confirmed by a subsequent measurement\*)
- Component 2: change of any component of the initial randomised regimen before W32 because of documented insufficient virologic response, defined as HIV-1 RNA reduction  $< 1 \log_{10}$  copies/ml by W18 or HIV-1 RNA  $\geq$  400 copies/ml at W24 (confirmed by a subsequent measurement\*)).
- Component 3: HIV-1 RNA  $\geq$  50 copies/ml (confirmed by a subsequent measurement\*) at any time after W32
- Component 4: death due to any cause
- Component 5: any new or recurrent AIDS defining event (category C events as defined in appendix 4) confirmed by the Endpoint Review Committee
- Component 6: any new serious non AIDS defining event, as defined in appendix 5, confirmed by the Endpoint Review Committee

\*In case of treatment modification for virological reasons, it is mandatory to take the retest sample before any treatment modification.

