### 3.2 Secondary endpoints

Secondary endpoints are:

- Time to loss of virologic response (TLOVR) by W48 and W96 defined as time to virologic failure (as defined in primary endpoint, components 1-3) or regimen discontinuation for any reason or death
- Time to virologic failure (as defined in primary endpoint, components 1, 2 and 3)
- Time to clinical failure (as defined in primary endpoint, components 4, 5 and 6)
- Time to permanent discontinuation of any component of the initial randomised regimen for treatment-limiting adverse event, i.e. intolerance or toxicity
- Time to discontinuation of any component of the initial randomised regimen for any reason
- Time to loss of virologic response by end of follow-up defined as time to virologic failure (as defined in primary endpoint, components 1-3) or regimen discontinuation for any reason or death
- Change in absolute CD4 count and in percentage from baseline
- Adverse events: number, nature and time to occurrence of clinical and laboratory grade 3 and 4 events
- Genotypic resistance at virologic failure
- Change in quality of life scores between W0 and W96

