## **7.9 Assessment of treatments**

### **7.9.1 Antiretroviral treatment**

At all study visits, the following details are recorded for any antiretroviral drugs, including the study drugs:

- commercial name of the product
- formulation
- dosage per unit
- prescribed dosage
- start date of this prescribed dosage
- stop date of this prescribed dosage
- reason for discontinuation

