## 7.12 Study regimen termination

Study regimen termination is defined by the definite discontinuation of any component of the initially allocated study regimen for any reason. The decision on regimen discontinuation should be taken based on clinical decision criteria and standard of care, and not on the protocol endpoints. The reason for regimen discontinuation and the date of discontinuation must be recorded in case record form.

The patient should receive appropriate 2nd line antiretroviral treatment after trial regimen discontinuation, based on current guidelines, patient's history and condition as well as co-medications.

Study regimen modifications should not lead to patient withdrawal from the trial: Patients discontinuing their study regimen have to be followed-up according to the scheduled trial visits until the end of the trial and all data should be collected (under the condition that informed consent has not been withdrawn).

If a patient wishes to discontinue trial treatment at any moment, investigators should explain the importance of remaining on trial follow-up, or - failing this - of allowing routine follow-up data to be used for trial purposes.

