### Regimen termination guidelines

Decision to discontinue a patient from the study regimen may be considered in the following circumstances:

- Insufficient virologic response:
  - HIV-1 RNA reduction < 1 log10 copies/ml at W04, W08, W12 or W18, or HIV-1 RNA ≥ 400 copies/ml at W24  
Any decision should only be taken after confirmation of the HIV-1 RNA level and after discussion with the regional CTU.
  - HIV-1 RNA ≥ 50 copies/ml by W48 (if suppression of HIV-1 RNA < 50 copies/ml never achieved).
- Confirmed rebound in HIV-1 RNA ≥ 50 copies/ml after initial suppression below 50 copies/ml.  
All patients having achieved a plasma viral load < 50 copies/ml at any time and having a subsequent viral load ≥ 50 copies/ml should be retested from 10 days to 4 weeks.
- Disease progression whilst on therapy.
- Withdrawal of patient consent.
- Unacceptable toxicity.
- Intercurrent illness which prevents further treatment, such as the need to start concomitant treatment with medication that is not compatible with the use of the study medications.
- Any change in the patient's condition, such as pregnancy, which justifies the discontinuation of treatment in the clinician's opinion.

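### After a missed W18 or W24 visit, section 9.2 judges insufficient response by regimen change alone; this conflicts with component 2 and can count a non-virologic switch as virologic failure

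*Protocol*

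**What the plan says.** Section 9.2, under the heading on intermittently missing HIV-1 RNA, covers a patient who missed W18 or W24. Whether insufficient response occurred at that visit "will be based on whether the regimen was changed at the next attended visit (week 24 or week 32"). No other condition is attached.

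Section 3.1 defines component 2 of the primary endpoint as a "change of any component of the initial randomised regimen before W32 because of documented insufficient virologic response". The thresholds are a fall of less than 1 log10 by W18 or a level of at least 400 copies/ml at W24, confirmed by a second measurement. A footnote adds that when treatment is modified for virological reasons, "it is mandatory to take the retest sample before any treatment modification".

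Section 3.2 places other discontinuations in separate secondary endpoints: "Time to permanent discontinuation of any component of the initial randomised regimen for treatment-limiting adverse event, i.e. intolerance or toxicity" and "Time to discontinuation of any component of the initial randomised regimen for any reason". The termination guidelines in section 7.12 list several non-virologic grounds for stopping, among them "Unacceptable toxicity", intercurrent illness and pregnancy.

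The reason for a change is collected. Section 7.9.1 lists "reason for discontinuation" among the items recorded for every antiretroviral drug, and section 7.12 states: "The reason for regimen discontinuation and the date of discontinuation must be recorded in case record form".

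**The concern.** The two sections give different tests for the same event. Section 3.1 needs a virologic cause with laboratory support. Section 9.2, for a patient with a missed visit, needs only a change. Take a patient who misses W18, has a drug replaced for intolerance and has suppressed virus at W24. Under 3.1 this patient has no event; under the literal text of 9.2 the patient has failed. The same false event enters time to virologic failure, which uses components 1 to 3.

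The error need not balance between arms. The trial is open-label. Section 2.5 says the new regimen might have advantages in toxicity and tolerability. Section 2.6 names rash as a risk of the raltegravir combination and renal dysfunction as a risk of tenofovir. Section 7.12.4 has a clearance-based discontinuation rule for tenofovir/emtricitabine only. An excess of false failures in the raltegravir arm works against non-inferiority; an excess in the control arm works in its favour.

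The planned sensitivity analyses do not isolate the problem. The 200 copies/ml analysis changes only the W32 and later criteria. The per-protocol analysis censors events after the randomised treatment stops, and it is not clear that this removes an event dated at the change itself.

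**Working it through.** **Step 1: the texts side by side.**

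| | Section 3.1, component 2 | Section 9.2, W18 or W24 missed |
|---|---|---|
| Regimen change needed | yes, before W32 | yes, as seen at the next attended visit |
| Reason for the change | insufficient virologic response | not mentioned |
| HIV-1 RNA evidence | threshold, confirmed | not mentioned |

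No other section restricts the 9.2 rule to virologic reasons.

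**Step 2: the plan's own power figure, as a benchmark.** The inputs from section 9.1 are a control failure rate of 20% at W96, a 9-point margin, 400 per arm, two-sided alpha 0.05 and 10% loss (stated for W144). With 10% loss, 400 × 0.9 = 360 per arm. SE = √(2 × 0.20 × 0.80 / 360) = 0.0298. Power = Φ(0.09/0.0298 − 1.96) = 85.5%, against the stated 85%. Without loss it is 88.9%. The design figure reproduces and is not in dispute.

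**Step 3: size of the misclassification.** The protocol gives neither of the two rates needed, so both are assumptions:
- m = share of an arm that misses W18 or W24, 2-10%;
- t = share of those with a non-virologic change seen at the next attended visit, 2-10%.

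False failures = m × t in percentage points, and 400 × m × t in patients per arm (in brackets):

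| m \ t | 2% | 5% | 10% |
|---|---|---|---|
| 2% | 0.04 (0.16) | 0.10 (0.4) | 0.20 (0.8) |
| 5% | 0.10 (0.4) | 0.25 (1.0) | 0.50 (2.0) |
| 10% | 0.20 (0.8) | 0.50 (2.0) | 1.00 (4.0) |

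Against the 400 × 0.20 = 80 failures expected per arm by W96, this is 0.2% to 5%. It slightly overstates the net excess, because some of these patients would fail later anyway.

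**Step 4: effect on the non-inferiority contrast if all false failures fall in one arm.** The true difference is taken as zero, with d the excess as a proportion and SE = √([0.20 × 0.80 + (0.20 + d)(0.80 − d)] / 360). The chance of declaring non-inferiority is Φ((0.09 − d)/SE − 1.96) if the excess is in the raltegravir arm, and Φ((0.09 + d)/SE − 1.96) if it is in the control arm.

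| Excess (points) | Raltegravir arm only | Control arm only |
|---|---|---|
| 0 | 85.5% | 85.5% |
| 0.25 | 83.3% | 87.2% |
| 0.5 | 81.0% | 88.7% |
| 1.0 | 75.8% | 91.4% |

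The last row is the extreme: both assumed rates at their top value and no false failure in the other arm.

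**The case against.** The best defence is that the 9.2 paragraph only fills a gap in the laboratory record and does not redefine the endpoint. Section 9.2 refers back to the endpoint definition (citing 3.2, although it stands in 3.1), so component 2's causal condition could be carried over. The reason for change is recorded, toxicity discontinuation has its own endpoint, and section 9.4 leaves detail to a separate analysis plan, which might apply a filter by reason. Component counts are also to be reported, so the events could be inspected.

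That reading is possible, but it is not what 9.2 says. The paragraph names regimen change as the basis for the judgement and stops there, so two analysts could classify the same patient differently. The protocol itself fixes this rule, and it sits badly with the protocol's own endpoint.

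The defence is right about scope. The rule reaches only patients who missed W18 or W24 and whose change is seen at the next attended visit. A reader might infer that early tolerability switching in general enters the primary endpoint. It does not: patients who attended both visits are judged by component 2 as written, and switches made well before W18 fit the rule poorly. Section 7.12.4, for example, calls for immediate discontinuation in possibly drug-related grade 3-4 rash.

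**Conclusion.** The conflict between 9.2 and component 2 is real and should be removed. Followed literally, the rule can turn a non-virologic switch after a missed visit into a virologic failure.

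The effect is probably small: about 0.04 to 1.0 percentage points per arm, resting wholly on the assumed 2-10% ranges, with the direction unknown. Planned sample size, event number and power are unaffected.

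A reader might infer a shift that uses up a material part of the 9-point margin, for instance by supposing that half of all tolerability switchers also miss a visit. The documents do not support this, because they give no switching or missed-visit rates. The supposition also strains against plausible attendance. With 8% switching, 4% of the arm would have to both switch and miss a visit. That is impossible if only 2% miss one, and if 5% do, it makes four in five of them switchers.

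**What to change.** Amend the missing-data paragraph of section 9.2. After a missed W18 or W24, component 2 is met only if the recorded reason for the regimen change is insufficient virologic response, supported by any confirmed HIV-1 RNA taken before the change where available. A change recorded for any other reason is not a component-2 event, and the patient continues to be assessed at W32 and later.

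Do not also require a threshold HIV-1 RNA at the next attended visit. Component 2 has no threshold at W32, which is the next visit when W24 is missed. A patient who switched for genuine virologic failure may already be suppressed on the new regimen, so the added condition would erase a true failure.

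The cost is one sentence in 9.2, carried into the analysis plan. It uses data the case report form already holds and should be settled before outcome data are compared by arm.

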#### **Sensitivity analyses for the primary endpoint**

A sensitivity analysis will be done with the per protocol population, censoring events after a patient stops the initial randomised trial treatment.

Moreover, the primary analysis will be repeated using a value of 200 copies/ml instead of 50 copies to determine virological failure at W32 and viral rebound after week 32.

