### 7.12.2 Management in the case of protocol-defined virologic failure

Protocol definition of confirmed virologic failure is occurrence of an HIV-1 RNA level  $\geq 50$  copies/ml in two consecutive measurements, the second one to be done from 10 days to 4 weeks at the latest, after virologic suppression (HIV-1 RNA  $< 50$  copies/ml) at any time.

All patients having achieved a plasma viral load  $< 50$  copies/ml at any time and having a subsequent viral load  $\geq 50$  copies/ml should be retested at the local laboratory from 10 days to 4 weeks.

The December 1 2009 version of guidelines from the U.S. DHHS Panel on Antiretroviral Guidelines for Adults and Adolescents [3] states that low level viremia between 50 and 200 copies/ml of HIV-1 RNA should not necessarily be considered as virologic failure or a reason to change treatment. A similar position is adopted by the European EACS guidelines, version 5, November 2009 [2]. Therefore, patients with viral loads between 50 and 200 copies/ml should continue their treatment regimen, unless there is a clear indication to change therapy, such as documented resistance or if the low-level viremia is prolonged. In such cases, investigators must contact their regional CTU to discuss any virological concern before changing/modifying regimens. It is recommended to change the regimen when the viral load is confirmed  $\geq 200$  copies/ml.

At first HIV-1 RNA  $\geq 500$  copies/ml at any time after visit W32, HIV-1 genotype is to be assessed in the local laboratory. In addition, 1 ml of plasma is to be stored and frozen at that timepoint (biobank). This sample may later be sent to the central laboratory for centralised genotypic analysis (see specific SOP on sample handling and shipment).

In any case, change of therapy is left at the discretion of the treating clinician after careful assessment of failure reasons and consequences (genotypic resistance testing). The decision on regimen discontinuation should be taken based on clinical decision criteria and standard of care, and not on the protocol endpoints. The patients should be offered an active antiretroviral combination (see 7.12.5) and follow-up be continued until completion of the trial.

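### The only per-protocol analysis censors at every stop of randomised treatment, so a virological stop before W32 outside component 2 can be informatively censored

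*Protocol*

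**What the plan says.** The Protocol's primary analysis (section 9.2) is by intention to treat in all randomised patients, with follow-up continuing after a regimen change (section 7.12). Two sensitivity analyses are named. One replaces 50 by 200 copies/ml. The other is the only per-protocol analysis: "A sensitivity analysis will be done with the per protocol population, censoring events after a patient stops the initial randomised trial treatment".

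Section 3.1 makes some stops primary events in themselves. Component 2 is a "change of any component of the initial randomised regimen before W32 because of documented insufficient virologic response", defined by a fall of less than 1 log10 by W18 or a confirmed value of at least 400 copies/ml at W24. Confirmed values of at least 50 copies/ml are events at W32 (component 1) and later (component 3). A footnote adds: "In case of treatment modification for virological reasons, it is mandatory to take the retest sample before any treatment modification".

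The regimen termination guidelines in section 7.12 are introduced by "Decision to discontinue a patient from the study regimen may be considered in the following circumstances". Their list includes "Confirmed rebound in HIV-1 RNA" to 50 copies/ml or more after suppression, with no time limit. Section 7.12.2 says "It is recommended to change the regimen when the viral load is confirmed" at 200 copies/ml or more. Section 7.9.1 records the stop date and the "reason for discontinuation" for every antiretroviral drug.

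**The concern.** Censoring at the stop is harmless only if those who stop would have had the same later failure risk on the regimen as those who continue. A patient taken off because the virus is rebounding plainly would not. If the protocol lets such patients stop before they can meet a primary component, the per-protocol analysis loses failures of the randomised regimen.

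In a non-inferiority trial the per-protocol analysis is read beside intention to treat because switching can dilute a real difference. A patient who rebounds at W12 or W18, is switched and is suppressed again by W32 is a non-event under intention to treat and censored per protocol. Neither 50-copy analysis of the primary endpoint then records the failure. If this happens more often in one arm, the check moves for reasons unrelated to the regimens' true difference.

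**Working it through.** **Step 1. Which virological stops are affected?**

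| Virological stop | Primary event? | Under the per-protocol rule |
|---|---|---|
| Before W32, fall below 1 log10 (W04 to W18) | Component 2, if *by W18* covers the earlier visits | Event coincides with the stop |
| Before W32, confirmed 400 or more at W24 | Component 2 | Event coincides with the stop |
| Before W32, confirmed rebound of 50 or more, neither limb met | None | Censored before the W32 assessment |
| At W32, confirmed 50 or more | Component 1, retest precedes modification | Kept |
| After W32, confirmed 50 or more | Component 3, while change is recommended at 200 or more | Normally kept |

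The third row is the gap. A rebound to a few hundred copies at W12 or W18 can still be more than 1 log10 below baseline, and the 400-copy limb applies only at W24.

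**Step 2. The plan's own figures.** These reproduce. The hazard ratio for 20% to 29% is ln(0.71)/ln(0.80) = 1.535 (stated 1.53). Events needed are 4 × (1.960 + 0.842)² / (ln 1.53)² = 174 by Schoenfeld and 179 by Freedman (stated 176). Power on the difference with 360 evaluable per arm (400 less 10%) is Φ(0.09/√(2 × 0.2 × 0.8/360) − 1.96) = 85.5% (stated 85%). No stated number is wrong.

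**Step 3. Effect of the gap, with the true difference at the margin.**

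*From section 9.1:* 400 per arm. Control failure is 20% = 2 (insufficient response) + 8 (W32) + 5 (later rebound) + 5 (clinical). The margin is 9 points.

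*Set here:* every part is multiplied by 29/20 = 1.45 in the raltegravir arm.

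*Assumed, in no document:* 15% unrelated stops by W96 in each arm. A share g of W32 failures and later rebounds is stopped for virological reasons ahead of the primary event, at 60-99% of the time to it.

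The patients exposed to g are 8 + 5 = 13% of controls (52 of 400) and 13 × 1.45 = 18.85% of the raltegravir arm (75.4 of 400). A trial passes if D + 1.96 × √(V₁ + V₀) < 0.09, where D is the Kaplan-Meier difference at W96 and V the Greenwood variance. There were 4,000 trials per row; mean estimates come from 400,000 patients per arm.

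| g control / RAL | Early stops per 400 | KM control, RAL (%) | Difference | Wrongly passes |
|---|---|---|---|---|
| 0 / 0 | 0 / 0 | 20.0, 29.1 | 9.05 | 2.2% |
| 5% / 5% | 2.6 / 3.8 | 19.4, 28.2 | 8.75 | 2.9% |
| 10% / 10% | 5.2 / 7.5 | 18.9, 27.4 | 8.55 | 3.4% |
| 20% / 20% | 10.4 / 15.1 | 17.7, 26.0 | 8.2 | 4.6% |
| 10% / 20% | 5.2 / 15.1 | 18.8, 25.9 | 7.2 | 8.4% |
| 5% / 20% | 2.6 / 15.1 | 19.5, 26.0 | 6.4 | 12.5% |
| 20% / 10% | 10.4 / 7.5 | 17.8, 27.5 | 9.7 | 1.3% |
| 20% / 5% | 10.4 / 3.8 | 17.9, 28.2 | 10.3 | 0.8% |

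The Monte Carlo standard error is √(0.022 × 0.978/4000) = 0.23 points at 2.2%, so the step to 2.9% is barely beyond noise. Because g also applies to rebounds after W32, the table reaches somewhat beyond the gap in step 1.

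**Step 4. Component 2 on the stop day.** If such events were censored rather than kept, with g = 0, the difference would be 8.7 points and the chance of wrongly passing 3.8%.

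**The case against.** The strongest reply is that the endpoint already catches most virological stops. Component 2 makes the change itself an event, the mandatory retest puts the confirming sample before the switch, and from W32 the event threshold lies below the level at which change is recommended. The rule removes only what comes after the stop. If W18 or W24 is missed, the judgement "will be based on whether the regimen was changed at the next attended visit", so a switch is still used. All of this stands and confines the point to stops before W32 outside component 2, plus any switch made without the retest.

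Three further replies also stand. The non-inferiority decision rests on intention to treat. Loss of virologic response, a secondary endpoint, counts every discontinuation as failure, although it pools virological stops with all others. Censoring at treatment stop is a conventional on-treatment analysis, and the definition of the per-protocol population may properly sit in the SAP.

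A reader might infer more than this.

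- *Stopped patients count as successes.* They do not. Kaplan-Meier censoring removes them from the risk set. In the 10%/20% row, simply losing the events would give 29 − 3.77 = 25.2% in the raltegravir arm, against the estimated 25.9%.
- *The rule always pulls the difference towards zero.* It does not. The last two rows go the other way.
- *The distortion is several points.* One can add virological stops of 2% and 6% to failures of 20% and 25% and compare about 5.5 with 9.0 points. But the 9.0 is 5 + 4 by construction, and no section supports those rates. The 17% discontinuation quoted in section 2.2.1 for the earlier darunavir trial is all-cause.

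Deaths and serious events after a toxicity stop do drop out of the per-protocol analysis. They count under intention to treat, and the protocol gives no basis for a grace window.

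**Conclusion.** The point holds in a narrow form. The single per-protocol analysis ignores the reason for stopping, and sections 3.1 and 7.12 together leave a class of early virological stops that is censored before W32. That censoring can be informative.

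Its direction is not established. It is anti-conservative if such stops are commoner with raltegravir (8-12% chance of wrongly passing under the shares assumed) and conservative if commoner in control (about 1%). With equal shares of 5-10% it is slight, about 3% against 2.2%. It is not exactly nil, because at the margin the worse arm has more failures to lose. These figures rest on the assumed g, its timing and 15% unrelated stops, and the documents fix none of these. This is a worthwhile improvement to a supporting analysis. The primary analysis is unaffected.

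**What to change.** In section 9.2, under the sensitivity analyses for the primary endpoint:

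1. State that a component 2 event dated on the day of the stop is kept as an event.
2. Add a second per-protocol version in which a stop of any randomised component whose recorded reason is virological counts as failure on the stop date. Other stops are censored as now. Show it beside the planned version.

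The cost is a sentence or two and one re-run on reasons and dates already collected under section 7.9.1. The drawback is that the recorded reason is the investigator's in an open-label trial, and that pre-W32 rebound is not a primary component. Both are reasons to show the two versions together rather than replace one with the other.
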